**Fig. 2 Fig2:**
[figure not shown]
Cluster Timeline

### Data management

The research team will keep the identifying key, linking the name to code numbers, in a secure location and only the study principal investigators (PI) of the study will have access to primary data. Research assistants will not enter any personally identifying details into the data set. Data will be collected using a password-protected table, from where data will be synchronized and uploaded in the Open Data Kit (ODK), saved on a private server, and transferred to a data-analytic computer program (STATA) without the identifying key. The site PI will conduct quality assurance checks on data collected by the research assistants on the tablet.

The data collected with other means, like qualitative data and other documentation (e.g., supervision forms and training reports), will be safely stored in locked cabinets at the site office. The qualitative data will be fully anonymized and coded and will not contain any identifying information. Results of this project will be published regardless of being negative or positive and submitted to peer-reviewed scientific journals.

### Data analyses plan

#### Statistical analyses

Analysis of quantitative outcomes, including the primary outcome of GHQ-12, will adopt the intention-to-treat approach whereby all participants will be analyzed according to the arm to which their ward was randomized. That is, even if intervention arm participants did not attend all Group PM+ sessions, the primary analysis will include them in the Group PM+ arm. The linear mixed effects modeling approach will be used to model participant-level score outcomes. More specifically, the two follow-up time points (midline and endline) will be analyzed within the same model. The following design variables will be included as fixed effects: arm, time (an indicator for the follow-up time-point), the arm-by-time interaction (to allow for different intervention effects at each of the two follow-up time-points), ward gender (to account for the stratified design), and the three covariates used in the constrained randomization procedure (i.e., access to mental health services, disaster risk, and rural/urban status). To increase statistical power, each participant’s baseline measure of the outcome will be adjusted for as a fixed effect [57]. To account for clustering by ward, a random intercept will be included for which the degree of clustering is allowed to differ for intervention and control arm clusters. Due to the repeated follow-up measurements on participants, a random intercept will be included for participant. In the event that baseline outcome data are missing, we will use a constrained longitudinal analysis approach whereby the baseline measure is also modeled as an outcome (rather than a covariate) and the baseline mean level is constrained to be equal between arms [57]. In this case, we will allow for changing correlation of outcomes over time by additionally including a random slope for each individual or by using an unstructured residual correlation matrix. For score outcomes for which the assumptions of the linear mixed model are violated, we will transform the outcomes (e.g., log-transformation) or adopt a bootstrap approach to estimate confidence intervals. Binary outcomes will be analyzed within the generalized estimating equations framework. Specifically, we will use the modified Poisson approach [58] assuming a Poisson outcome distribution, with an exchangeable working correlation matrix and robust standard errors to account for the outcome model misspecification (i.e., Poisson instead of binomial). Such an approach has been shown to be preferable to a binomial regression model for clustered outcome data [58]. A log link will be used to obtain risk ratios and an identity link to obtain risk differences and the mean model will include the same terms as the models for the continuous outcomes.

Additional supportive analyses will test robustness to missing outcomes, to baseline covariate imbalance, and to the combination of both. Specifically, the supportive analyses will include the following three approaches: (1) analyses that account for any baseline covariates that are predictive of missing outcomes, (2) analyses that account for any baseline covariates identified to be imbalanced between treatment arms, and (3) analyses that combine both approaches (1, 2), i.e., that account for all baseline covariates identified to be predictive of missing outcomes or to be imbalanced. For approach (1) to assess robustness to missing outcome patterns, if the probability of missingness is only related to the baseline covariates in the model, then these adjusted analyses will provide valid estimates of the intervention effect having accounted for the missing data patterns.

Sub-group analyses will assess whether there are differing intervention effects according to the following variables: gender and baseline depressive symptoms. To do so, the model will include an indicator for the sub-group variable and interactions between that indicator and intervention arm and time-point. Baseline depressive symptoms will be included in the model as a binary variable indicating whether the participant met the cutoff score for depressive disorder, specifically a baseline PHQ-9 score of 10. These analyses are exploratory in nature as the study is not powered to detect such effects. Adherence in the intervention arm will be quantified through the number of sessions attended. Similarly, within the intervention arm, we will examine potential differences in intervention due to different facilitators. To do so, we will analyze outcomes in intervention arm only and see its relationship with facilitator. Likewise, within the intervention arm, we will examine whether estimated outcomes are different for those who completed all five sessions vs. those who completed fewer sessions.

We hypothesize that skills acquired will mediate any impact of the intervention. To this end, we will perform a mediation analysis within the framework outlined by Zhang et al. [59] that accounts for the multilevel (i.e., clustered) data structure. We will use the midline measure of the *Reducing Tension Checklist* as the mediating variable and the endline time-point for outcomes of interest. We note two important features of this analysis: (1) we have selected the midline measure for the hypothesized mediating variable to ensure that it precedes the outcome measure in time in order to be able to make stronger causal claims than we would were the mediator and outcome measured at the same point in time, and (2) we will ensure that potential confounders of the mediator–outcome relationship are accounted for in the analysis.

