Community psychosocial workers (CPSWs) are trained as Group PM+ facilitators [10]. CPSWs are a cadre of community health workers that have a long track record in providing psychosocial support in Nepal [19]. For this study individuals from the community will be recruited to become new CPSWs. Fifteen local community women and men who have completed higher secondary school (equivalent of 12th grade education) from the study region will be selected based on their basic communication skills as reflected through the interviews, management and organization skills, interest and motivation to serve community people, and commitment to work in the given time. They are then given a 10-day basic CPSW training, with a standard curriculum developed by TPO Nepal. The CPSW training includes an overview of psychosocial concepts, cause and effects of psychosocial issues, basic communication skills, common mental health problems in communities, group facilitation skills, and psychoeducation. Competency is evaluated before and after the CPSW training with a standardized role play assessment tool (ENACT) that has been developed in Nepal and used for non-specialists in humanitarian settings [20].

The CPSW training is followed by a 10-day Group PM+ training using the adapted manual and other intervention materials. Group PM+ is named *Khulla Man* (“open heart-mind” in Nepali), which is consistent with Nepali ethnopsychological models of distress, trauma, and recovery. The Group PM+ training includes learning about the impact of adversity on mental health, basic counseling skills, how to deliver the content of the Group PM+ manual, group management skills and self-care. Competency is assessed with ENACT again at the conclusion of the PM+ training, and fidelity is assessed with a PM+ specific checklist.

After completing PM+ training, three rounds of practice sessions will be completed by each CPSW in an adjoining district that is not a part of the study area. Competency assessments and supervision will be conducted during these practice sessions. Based on ENACT pre and post scores, clinical judgment during the PM+ practice sessions, assessments using the fidelity sheet, and the PM+ competency criteria, 12 CPSWs (ten female and two male) out of 15 will be selected. In regards to ENACT, the CPSW who scores the lowest points, i.e., 1 (Need improvement) for each item, will be removed from the study.

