### Randomization

The unit of randomization is the ward (i.e., the cluster), as this is the smallest unit of administration in Nepal. This unit was selected to ensure a sufficient number of clusters, as there are only 17 municipalities/villages in the district, which would be the next possible level of randomization. Municipalities with mainly non-Nepali speaking inhabitants will be excluded. A total of 72 wards will be selected for participation with a target sample size of eight participants enrolled per ward (see rationale below in the “Sample size justification” section). Then, for the 36 wards randomly allocated to Group PM+, a single group of eight participants will be formed in each ward. As indicated above, of these 72 wards, 14 will be selected as “male” wards and 58 as “female” wards to reflect differences in uptake of services by males compared to uptake by females, as observed in earlier studies conducted by our team (see above). As such, the overall estimated intervention effect will reflect such a 1:4 ratio of males:females should the intervention be scaled up more broadly. Furthermore, as noted above, we will not take a random sample of 14 wards as “male” since it is important that the selected wards are such that whichever seven are randomly allocated to Group PM+ are sufficiently close in proximity so that it will be reasonably straightforward for two male CPSWs to lead the seven male Group PM+ groups (i.e., one in each of the “male” Group PM wards).

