### Sample size justification

The c-RCT was designed to have at least 90% power to detect moderate effect sizes of 0.46 for the primary outcome of individual psychological distress, measured by the GHQ-12 questionnaire (see details below in the “Outcome Measures” section) at the primary time point of follow-up 20 ± 1 weeks after baseline for the control arm participants, and 12 + 1–2 weeks after the time of the final group session for the Group PM+ arm participants (i.e., endline). An effect size of 0.46 would correspond to between-arm differences of 3.2 units in mean GHQ-12 for an overall standard deviation of 7 units, a conservative assumption based on data from our pilot c-RCT [28]. Power was calculated in R software (version 3.4.2) by programming a standard calculation for a comparison of two means in a c-RCT with 72 clusters assuming a two-tailed 5% significance level [29]. It was additionally assumed that eight participants would be enrolled in each ward, and that up to two participants per ward would drop out before outcomes were measured (a conservative assumption for the purposes of the power calculation). Clustering of outcomes by ward was assumed to be relatively large with an interclass correlation coefficient (ICC) of 0.2 based on baseline data from a cohort study in the Chitwan district used in the PRIME study [22]. Although clustering in the EUC wards is anticipated to be lower than the assumed 0.2 in the Group PM+ wards because EUC participants will not meet in groups, we conservatively assume the same levels in both arms for the purposes of the power calculation.

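### The primary model has no facilitator level although 12 facilitators lead the 36 PM+ groups, so if facilitators differ the standard error of the primary contrast is understated

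*Protocol article*

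**What the plan says.** All places are in the protocol article.

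- **Delivery.** Group PM+ intervention: "12 CPSWs (ten female and two male) out of 15 will be selected", with facilitators matched to the gender of the group. Randomization: one group is formed in each of the 36 PM+ wards, and the male wards are chosen close together so that it is feasible for "two male CPSWs to lead the seven male Group PM+ groups". That leaves 36 − 7 = 29 female groups for ten female CPSWs.
- **Primary model.** Statistical analyses: a linear mixed model covers both follow-up times. Its random effects are a ward intercept ("To account for clustering by ward, a random intercept will be included for which the degree of clustering is allowed to differ" between arms) and a participant intercept. No facilitator term is listed.
- **Facilitators.** The same section says that, within the PM+ arm, "we will examine potential differences in intervention due to different facilitators". This uses intervention-arm data only.
- **Power.** Sample size justification: "The c-RCT was designed to have at least 90% power to detect moderate effect sizes of 0.46 for the primary outcome", from "a standard calculation for a comparison of two means in a c-RCT with 72 clusters assuming a two-tailed 5% significance level". It assumes eight participants enrolled per ward, up to two lost, and a ward ICC of 0.2 in both arms. Facilitators do not enter the calculation.

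**The concern.** Two PM+ wards led by the same CPSW share whatever that CPSW does better or worse than colleagues, so their mean outcomes are correlated to the extent that facilitators differ. A facilitator component averages over 12 units, but the planned model averages it over 36.

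Letting the ward variance differ by arm does not help. It lets facilitator variance appear as extra ward variance in PM+, but still divides it by 36. The within-arm facilitator analysis may describe the differences, but it leaves the primary standard error unchanged.

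At stake are the confidence interval and p-value for the primary contrast at endline. The EUC arm has no matching level: its family meeting is given by community informants, one per ward.

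**Working it through.** **Inputs from the protocol article.** Effect size 0.46 ("between-arm differences of 3.2 units in mean GHQ-12 for an overall standard deviation of 7 units"; 3.2/7 = 0.457); two-sided 5%; 36 wards per arm; 8 − 2 = 6 analysed per ward; ICC 0.2 in both arms; 12 facilitators.

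**Assumed, because the documents do not give it.** The facilitator share f of total variance, counted inside the 0.2 ward-level share in PM+, and an even split of three groups per facilitator.

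**Step 1: reproduce the stated power.** With total variance 1, the variance of the difference is 2 × (0.2 + 0.8/6)/36 = 0.018519, so SE = 0.1361. Then 0.46/0.1361 = 3.380, and power is 92.2% (normal) or 91.5% (t, 70 df). The claim of at least 90% reproduces, with about two points to spare.

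**Step 2: add the facilitator level.** In PM+ the variance of the arm mean becomes f/12 + (0.2 − f)/36 + 0.8/216. Compared with step 1 this adds f × (1/12 − 1/36) = f/18.

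**Step 3: the standard error the planned model would report.** It is based on the spread of the 36 PM+ ward means as if they were independent. It stays at about 0.136, falling very slightly to 0.1355 at f = 0.10 because shared facilitators make some ward means alike.

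| f | Variance of difference | True SE | True SE / 0.1361 | Type I error of planned test | Power with the true SE, normal / t (70 df) |
|---|---|---|---|---|---|
| 0 | 0.018519 | 0.1361 | 1.000 | 5.0% | 92.2% / 91.5% |
| 0.01 | 0.019074 | 0.1381 | 1.015 | 5.4% | 91.5% / 90.7% |
| 0.02 | 0.019630 | 0.1401 | 1.030 | 5.7% | 90.7% / 89.9% |
| 0.05 | 0.021296 | 0.1459 | 1.072 | 6.8% | 88.3% / 87.5% |
| 0.10 | 0.024074 | 0.1552 | 1.140 | 8.7% | 84.2% / 83.2% |

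Type I error is the two-sided normal tail beyond 1.96 × (model SE / true SE). Power crosses 90% at f of about 0.02 to 0.03.

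**Step 4: checks.**
- An uneven split (nine female CPSWs with 3 groups and one with 2; male CPSWs with 4 and 3) gives Σg²/36² = 110/1296 = 0.085 in place of 1/12 = 0.083. Results barely change.
- A simulation of ward means with that split, analysed without a facilitator term (200,000 runs), gives type I error of 5.7%, 6.8% and 8.8% at f = 0.02, 0.05 and 0.10. The uncorrected test rejects in 90.9%, 90.0% and 88.7% of runs at effect 0.46, but only at that inflated error rate.
- With Satterthwaite degrees of freedom and the uneven split, power is 88.9%, 86.0% and 81.1%.
- If two CPSWs co-led each group in six fixed pairs, f would average over six units, and power at f = 0.02 would be 88.3% (normal).

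**The case against.** **The size is conditional.** No facilitator variance is given. At f = 0 there is no harm, and at 0.01 the true SE is only 1.5% above the planned one. The CPSWs are selected on competency, trained together, supervised twice weekly and checked for fidelity, all of which plausibly reduces differences between them. Planning to look for such differences is not evidence that they are material. This stands: the missing term is a fact of the document, but its effect is not.

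**The power calculation has slack.** It analyses six of eight participants, uses 0.2 in EUC where lower clustering is expected, and takes no credit for baseline adjustment. At f = 0.05 (uneven split, normal / t), power is 91.5% / about 90.8% with an EUC ICC of 0.1, and 90.9% / 90.1% with all eight analysed. It is 93.0% / 92.3% if baseline and outcome correlate at 0.4 (assumed; all variance scaled by 1 − 0.4² = 0.84). A reader might infer that the 90% power claim is false; the documents do not support that. None of this slack, however, repairs an understated standard error or the type I error.

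**The ICC wording.** A reader might also fault "we conservatively assume the same levels in both arms for the purposes of the power calculation". In context the word describes applying the PM+ value to EUC wards, where less clustering is anticipated. That is conservative, and no criticism is made of it.

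**Facilitators as fixed.** If the conclusion is confined to these 12 CPSWs, omitting a random facilitator effect is defensible. But the Background and Discussion tie the result to global release of the manual, which points to inference beyond them.

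**Conclusion.** The point holds in conditional form. The protocol itself states that facilitators are shared across wards and specifies a primary model that leaves this level out. For any facilitator variance above zero, and for inference beyond these 12 CPSWs, the primary standard error is too small: by a few per cent at a share of 0.02 to 0.05, and about 14% at 0.10. The main consequence is an interval that is too narrow and a type I error above 5%. The power consequence is secondary: the stated figure is correct on its own assumptions, and falls below 90% at a share of about 0.02 to 0.03 only if the plan's other margins do not materialise.

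The missing term is certain. The size rests on the assumed share, on its being counted inside the 0.2, and on one facilitator leading about three groups. The allocation of female CPSWs is not stated, and the supervision text leaves co-leading possible.

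**What to change.** 1. Add a facilitator random intercept in the PM+ arm only (participant within ward within facilitator) to the primary model, or at minimum as a prespecified sensitivity analysis of the primary outcome. Use small-sample degrees of freedom such as Satterthwaite, because a variance from 12 facilitators, two of them male, is poorly estimated and may come out at zero when it is not.
2. State who leads each group. If groups are co-led, use a multiple-membership term in place of strict nesting.
3. Keep the planned within-arm facilitator comparison. It already requires outcomes to be linked to facilitator, so no new data should be needed.
4. Add a sentence to the sample size justification giving power over a range of facilitator shares, naming the approximation used. The existing ICC wording can stay.

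The cost is one more variance term, a slightly wider confidence interval, an imprecise facilitator variance and a somewhat less favourable power statement.

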***Secondary outcomes (participants)***						
Depression symptoms	*Depression symptoms (PHQ)*	Participants rate depression symptoms over past two weeks		X	X	X
Daily functioning	*WHODAS*	Participants rate their ability to engage in daily activities		X	X	X
Post-traumatic stress symptoms	*PTSD Checklist for DSM5 (PCL-5)*	Participants rate their post-traumatic stress symptoms on a scale		X	X	X
Perceived social support	*Multidimensional Scale of Perceived Social Support (MSPSS)*	Participants assess their own connectedness with close family, friends and other forms of support		X	X	X
Somatic symptoms	*Somatic Symptom Scale-8 (SSS-8)*	Participants rate how much they have been bothered by somatic symptoms		X	X	X
General psychological distress	*Heart-mind*	Participants note if they have had any *“man ko samasya”* or heart-mind problems recently			X	X

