**Table 3 Tab3:**
[figure not shown]
Schedule of enrollment, interventions, and assessments for Group PM+

The WHO Disability Assessment Scale (WHODAS) is a generic instrument assessing health and disability in adults. It assesses difficulties that people are experiencing during the last 30 days, due to their illness, across six domains of functioning (cognition, mobility, self-care, getting along, life activities, and participation). Difficulties are scored on a five-point Likert scale of: not at all difficult, a little difficult, sometimes difficult, very difficult, or always difficult. The WHODAS can be used with all diseases and across cultures. The scale has been previously used in Nepal and has a good internal consistency between items (α = 0.90) and validity with multiple mental health measures for depression (*r* = 0.616, *p* < 0.001), anxiety (*r* = 0.624, *p* < 0.001), and PTSD (*r* = 0.499, *p* < 0.001) [4, 44].

The Patient Health Questionnaire (PHQ-9) is a ten-item instrument measuring symptom depression [40]. It has been translated and clinically validated in a primary care population in Chitwan, Nepal: the validated cut-off score of ≥ 10 (sensitivity = 0.94, specificity = 0.80, PPV = 0.42, NPV = 0.99, positive likelihood ratio = 4.62, and negative likelihood ratio = 0.07) [30].

The original Post-traumatic stress disorder Check List (PCL)-5 is a 20-item checklist corresponding with the 20 DSM IV PTSD symptoms. To diminish the burden of questionnaires administered by participants in this study, the eight-item version will be used. This was shown in a recent study to have comparable diagnostic utility to the 20-item PCL-5 [45] and has been used in Nepal and will be used in this study to diminish the burden of questionnaires administered by participants [46].

The Multidimensional Scale of Perceived Social Support (MSPSS) [42] is a self-rating tool of perceived social support from three categories of support: family, friends, and significant other. It has been locally adapted [47] and validated to use in Nepal [48]. The MSPSS consists of 12 questions that are rated on a five-point Likert scale ranging from 1 (“very strongly disagree”) to 5 (“very strongly agree”). Higher scores indicate higher perceived levels of social support.

The Somatic Symptom Scale (SSS) is an eight-item patient-reported outcome measure of somatic symptom burden [43] that has been translated and adapted using a standard cross-cultural approach [49].

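### The exploratory test of effect modification by baseline depression uses only a PHQ-9 split at 10; if moderation is roughly linear in an approximately normal score, this loses at least about 36% of the moderator information

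*Protocol article*

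**What the plan says.** The Statistical analyses section of the protocol article plans sub-group analyses by gender and by baseline depressive symptoms. The test is set out as follows: "the model will include an indicator for the sub-group variable and interactions between that indicator and intervention arm and time-point". For depression the coding is fixed: "Baseline depressive symptoms will be included in the model as a binary variable indicating whether the participant met the cutoff score for depressive disorder". The threshold that defines this indicator is then given as "specifically a baseline PHQ-9 score of 10".

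The cut comes from the description of the PHQ-9 under Secondary outcomes, which cites "the validated cut-off score of ≥ 10" from a clinical validation in a Nepali primary care population. Table 2 lists the PHQ ("Participants rate depression symptoms over past two weeks") at baseline, midline and endline, so the full baseline score is available.

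The protocol is open about the status of these analyses: "These analyses are exploratory in nature as the study is not powered to detect such effects". It describes no interaction that uses the PHQ-9 as a score, and it gives no expected baseline distribution or share of participants at or above 10.

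**The concern.** The sub-group question concerns depressive symptoms, which are graded. With a single indicator as moderator, participants scoring 9 and 10 count as different, while those scoring 10 and 25 count as alike. A validated screening threshold is a good reason to present effects on either side of it. Its validation concerns how well it detects depression and does not show that the effect of Group PM+ changes there.

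At stake is what the trial can say about whether benefit varies with initial depression. If benefit rises or falls steadily with severity, the split makes a weak test weaker and ties the answer to one cut point. A null result would then be even harder to interpret.

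**Working it through.** **1. The protocol's own power figure.** The only stated power is for the main effect on GHQ-12: "at least 90% power to detect moderate effect sizes of 0.46", equated with "between-arm differences of 3.2 units in mean GHQ-12 for an overall standard deviation of 7 units". The inputs from Sample size justification are 72 wards (36 per arm), 8 enrolled per ward with up to 2 lost (6 analysed), ICC 0.2, and two-sided 5%.

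- Design effect = 1 + (6 − 1) × 0.2 = 2.0.
- Effective n per arm = 36 × 6 / 2.0 = 108.
- Standard error of the standardised difference = √(2/108) = 0.136.
- At 0.46: power = Φ(0.46/0.136 − 1.96) = 92.2%, or 91.5% with a t reference on 70 df.
- At 3.2/7 = 0.457: 91.9%, or 91.2% with t.

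The stated figure reproduces. There is no corresponding figure for the PHQ-9 interaction.

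**2. Information kept by the split.** Assume, because the protocol does not say, an approximately normal baseline score and an intervention effect that changes linearly with it. With a share p at or above the cut, z the matching normal quantile and φ the normal density, the squared correlation between score and indicator is

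retained = φ(z)² / [p(1 − p)].

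This is the fraction of moderator information the indicator keeps.

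| Share at or above 10 (assumed) | φ(z)² / [p(1 − p)] | Retained | Lost |
|---|---|---|---|
| 50% | 0.1592 / 0.25 | 0.637 | 36% |
| 70% | 0.1209 / 0.21 | 0.576 | 42% |
| 80% | 0.0784 / 0.16 | 0.490 | 51% |
| 85% | 0.0544 / 0.1275 | 0.426 | 57% |
| 90% | 0.0308 / 0.09 | 0.342 | 66% |

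Under these assumptions the even split is the best case, so about 36% is the minimum. There is no matching maximum, because the loss keeps growing as the split becomes more uneven.

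**3. The same in power terms.** Suppose the continuous interaction had 80% power, so that its expected z statistic is 1.960 + 0.842 = 2.802. The indicator multiplies this by √retained. At 50/50, 2.802 × 0.798 = 2.235, and power = Φ(2.235 − 1.960) = 61%. The same step gives 57% at 70/30, 50% at 80/20 and 45% at 85/15. These ratios do not depend on the number analysed or the residual SD: 432 or 576 participants, and SD 7 or 7 × √0.8 = 6.26, give the same results.

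**4. Sensitivity to normality.** Integer scores simulated on 0 to 27, still with linear moderation:

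- rounded normal, mean 10, SD 5: share 54%, loss 35%;
- rounded normal, mean 13, SD 5: share 76%, loss 47%;
- rounded normal, mean 15, SD 5: share 87%, loss 59%;
- skewed (gamma), mean 10: share 47%, loss 38%;
- skewed (gamma), mean 13: share 72%, loss 52%.

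The size of the loss is not an artefact of exact normality. It does depend on linearity. If the effect were a step at 10, the indicator would be the correct coding and would lose nothing, and the linear score would carry the loss instead.

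**The case against.** The case for leaving the plan alone is reasonable. The cut is fixed in advance and locally validated, so there is no risk of a threshold chosen after seeing the data. A contrast between people who do and do not screen positive for depression is easy for decision-makers to read. Moderation by depression is not among the hypotheses under Objectives; it appears only as a sub-group analysis that the protocol declares exploratory and unpowered. The continuous alternative makes its own assumption about shape. A fuller analysis plan may also add a continuous model, and the article's silence on one does not show that it is absent.

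All of this stands, and it keeps the point minor. It does not make the split the better test. Advance specification removes the risk of cut-point selection but not the loss of information, and an admitted lack of power is a reason not to give up more of it. The binary coding is itself something the article states, not a detail it leaves open.

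A reader might infer more than the protocol supports:

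- That a fixed percentage, such as 36% to 57%, will be lost in this trial. That range is simply what assumed shares of 50% to 85% produce. The protocol gives no share, and the loss could be above that range or nil.
- That the analysis is biased or the cut arbitrary. Nothing shows either.
- That depression severity is ignored throughout. The models adjust for the baseline measure of the outcome, so when PHQ is the outcome its baseline also enters as an adjustment covariate. The loss concerns the moderator term.

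**Conclusion.** The point holds as a minor, optional improvement to an exploratory analysis. The protocol tests effect modification by baseline depressive symptoms with a yes/no indicator, although the full score is collected. The loss of at least about 36% is conditional on two assumptions, an approximately normal score and roughly linear moderation; any larger figure also depends on the unknown share of participants at or above 10. The sample size, the primary GHQ-12 analysis and every confirmatory claim are unaffected.

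**What to change.** In the sub-group paragraph of Statistical analyses, make the moderator test the interaction of centred continuous baseline PHQ-9 with arm and time-point. Keep the cut at 10 for presentation, still reporting the pre-specified effects below and at or above it. Keep the exploratory label.

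The change needs no new data, visits or participants, only wording. Its downside is the assumption of an approximately linear interaction. A quadratic or spline term can be added as a check, but it will have low power, so a non-significant result should not be read as proof of linearity. Showing the effects on either side of 10 alongside the continuous test gives readers some protection if the true pattern is closer to a step.
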